Immediately after recruitment to the trial, the mother or guardian of each study child will be provided with a long lasting, insecticide treated net (LLIN) that is marked with an identification number. Instructions will be given to the parent or guardian on how to use the net and the importance of using the net on the bed/sleeping place of the study child will be emphasized. If a child already has a net, this will be replaced and the old net returned to the family for their use. Utilisation of LLINs by study children will be monitored during home visits made to collect blood films (see below) and during the cross-sectional survey conducted at the end of the malaria transmission season.

*Intermittent preventive treatment*

Study children will be treated with a course of SP + AQ or matching placebos on three occasions during the malaria transmission season. Drugs will be pre-packaged to facilitate administration. Monthly doses will be timed to cover the peak transmission season at each site, July/August/September in Burkina Faso and Aug/Sept/Oct in Mali. Doses of AQ and SP will be based on weight as shown in Table 2. AQ will administered on the base of 10 mg/kg daily for 3 days and SP will administered as a single dose of 25mg/kg of sulphadoxine + 1.25 mg of pyrimethamine. Full tablets containing the exact daily dose (AQ) or the dose for a full course (SP) will be manufactured to avoid having to split tablets which may lead to administration of inadequate doses.

**Table 2**. Dosage of study drugs.

Weight groups Amodiaquine* SP**

Tablets (Daily dose) tablets (single dose) **

Sulfadoxine Pyrimethamine

5-9 kg 70 mg 175 mg 8.75 mg

10-18 kg 140 mg 350 mg 17.5 mg

19 kg+ 220 mg 550 mg 26.25 mg

Note. * Tablet given for 3 days;  ** tablet given for 1 day

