Drugs will be given under observation at a central point in the village. Children will be asked to stay at the distribution point for 30 minutes after drug administration. If vomiting occurs during this period, drugs will be re-administered. If vomiting recurs this will be noted but the drugs will not be given on a third occasion. Such children will not be excluded from the trial and they will be eligible to receive drugs at the subsequent monthly treatment. If a child misses the day set for treatment, a home visit will be made to enquire why the child was not brought for treatment and this will be recorded. If the family would like the child to continue with treatment but he or she was unable to attend on the specified day, then the first dose of treatment will be reoffered within 3 days and treatment must be completed within a maximum of 7 days after the designated date for each round. A dose missed on second of third day of treatment must be administered with 48 hours of the planned date. Thus, no child will receive two doses of SP + AQ at an interval of less than three weeks.

*Safety of IPT with SP and AQ*

Safety of SP and AQ will be monitored in all children on days 0, 1 and 2 of treatment administration and on day 3 (day after the last dose of treatment for each treatment round). .At the second and third treatment rounds, the families of each study child will be asked whether the child has had any symptoms that might have been drug related since the previous drug administration round.

Serious adverse events, including deaths and hospital admissions, will be recorded throughout the 18 months of surveillance. The likely relationship of the adverse event to drug administration will be determined according to standard criteria. Serious adverse effects will be reported to the Data Safety and Monitoring Board (DSMB) within a period specified by the board.

*Surveillance for malaria*

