At the end of the malaria transmission season, a cross sectional survey will be undertaken at which each child will be examined, their height, arm circumference and weight recorded and a finger prick blood sample obtained for determination of Hb concentration, preparation of blood films and collection of a filter paper sample for subsequent studies on the prevalence of molecular markers of resistance.

Any death in a study child will be investigated within a month of death using the post-mortem questionnaire technique.

*Surveillance for ‘rebound’ malaria*

Passive surveillance for malaria will be continued during the dry season and the subsequent malaria transmission season to determine if IPT impairs the development of natural immunity to malaria, reflected in an increase in the incidence of malaria in children who have received IPT during the previous year (rebound malaria). Identical surveillance techniques to those described above, including a final cross-sectional survey, will be used during the second year of observation.

*Surveillance for drug resistance*

Molecular markers associated with resistance to amodiaquine and to SP will be investigated in children with malaria parasitemia before and after the peak malaria transmission season to determine whether resistant parasites are selected by IPT. At baseline (before treatment administration) children will be sampled from a census database list for the prevalence of markers of resistance to SP and AQ. These children will have a clinical examination, a thick and thin blood film and filter paper blood spot prepared, and haemoglobin concentration will be determined. Samples will be collected as set out in Table 3.

**Table 3.** Samples for testing for molecular markers at each site.

Study group Number of samples Number likely to be Number for

collected positive for malaria molecular assays

Year 1

Random sample 750 300 150**

children < 5 years

before intervention *

Cross-sectional

survey – post intervention

IPT 1500 300 150**

Placebo 1500 750 150**

Year 2

Cross-sectional

survey

IPT 1500 750 150**

Placebo 1500 750 150**

Notes.

* These children will not be included in the trial but will come from the same area.

** Random sample from the positive blood samples available.

Thus, during the first year of the study approximately 450 samples will be tested from each site and during the second year 300 giving a total of 1,500 over the two years of the trial.

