**2008**

April - June Preparation of trial sites.

July - Nov Administration of IPT and surveillance for malaria.

December Laboratory analyses.

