4.1 The number of children to be enrolled in the trial in Navrongo has been split between MRTC Mali and CNRFP, Burkina Faso as the trial will now be conducted in these two sites only. The number of children to enrolled at each of these two sites is now increased to 3,000 children (1,500 per arm). The initial sample size of 2000 children per site was estimated to have adequate power to measure the protective efficacy of IPTc on malaria morbidity at each site and to pool the data from all three sites (6,000 children) to measure the impact of IPTc on admission to hospital with severe malaria. Therefore, in order to have adequate power to measure the effect of IPTc on hospital admissions with malaria, we have to increase the sample size from 2,000 to 3,000 in Burkina Faso and Mali.

4.2 The number of children to be enrolled in the weekly and the monthly surveys for the effect of IPTc on the prevalence of malaria infection and the number of samples to be analysed per site to assess the impact of IPTc on the prevalence of markers of resistance to SP and AQ have been re-adjusted by redistributing samples that were to be collected at the Navrongo site between CNRFP and MRTC. Thus site will collect 2500 more samples over the study period (see table 3 below).

1. Baseline survey of markers of resistance to SP and AQ

A random sample of children from the study villages’ census lists will be selected for the baseline survey of the prevalence of markers of resistance to SP and AQ (about 400-500 children per site). Children who will be involved in this survey will not take part in the trial of intermittent preventive treatment, but will be given and ITN. Initially, these children were to be recruited from neighbouring villages.

1. Safety of SP and AQ (Monitoring of adverse events)

The initial plan was to conduct weekly visits in a random sample of 100 children to monitor adverse events. It has now been amended that adverse events will be assessed on days 0, 1 and 2 of IPTc administration and the day after the last dose of IPTc administration in all children enrolled in the study. Adverse events that may occur after day 3 post IPTc will be recorded on day 0 of the next round of IPTc administration. This option provides the opportunity for monitoring adverse events in all study children.

1. Intermittent Preventive Treatment administration

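### Late non-serious symptoms are asked about only at the next treatment round, so no such enquiry is scheduled after the third and last course

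*Combined protocol and SAP*

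**What the plan says.** Under Intermittent preventive treatment in section IV, the regimen is fixed at three rounds: "Study children will be treated with a course of SP + AQ or matching placebos on three occasions during the malaria transmission season". The months are "July/August/September in Burkina Faso and Aug/Sept/Oct in Mali".

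The section on safety of IPT with SP and AQ has every child monitored on days 0, 1 and 2 of each round and on day 3, the day after the last dose. For anything later it relies on recall: "At the second and third treatment rounds, the families of each study child will be asked whether the child has had any symptoms" that might be attributed to the drugs, looking back to the previous round. The item on adverse event monitoring in the protocol amendments describes the same mechanism: "Adverse events that may occur after day 3 post IPTc will be recorded on day 0 of the next round of IPTc administration".

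The same safety section records serious adverse events, including deaths and admissions, throughout 18 months of surveillance. Section V sends serious events and possibly drug-related grade 3 events to the DSMB and has other events summarised by group.

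After the last round, all children are next due to be seen at the survey described under Surveillance for malaria: "At the end of the malaria transmission season, a cross sectional survey will be undertaken at which each child will be examined". The content listed there is anthropometry, haemoglobin, blood films and a filter paper sample. The section on insecticide treated nets adds that net use is checked "during the cross-sectional survey conducted at the end of the malaria transmission season".

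**The concern.** The late enquiry depends on there being a next round. That works after courses 1 and 2 and cannot work after course 3. A plan followed exactly would give the DSMB group summaries with an all-child late enquiry for two courses. For the third they would hold days 0 to 3 plus whatever happened to reach a health centre. Unless the tables are labelled, few late symptoms after course 3 could be read as good tolerability when nobody was scheduled to ask.

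At stake is the completeness of late tolerability data for a preventive drug given to children under five. It includes any grade 3 reaction that did not bring the child to care, since section V wants possibly drug-related grade 3 events reported but names no collection point after the last round. Efficacy is not at stake.

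**Working it through.** The plan states no figure on this point, so the check sets the schedule of contacts against the courses and counts.

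**Step 1. Which courses have a late enquiry?**

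| Course | Days 0–3, all children | Later symptoms, all children |
| --- | --- | --- |
| 1 | yes | asked at round 2 |
| 2 | yes | asked at round 3 |
| 3 | yes | none scheduled |

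**Step 2. Do other contacts after round 3 fill the gap?**

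- Health centres (Surveillance for malaria): project staff identify study children who attend, take their temperature, and test those with fever or recent fever. This depends on attendance and is aimed at malaria. No drug-related symptom enquiry is stated.
- Weekly home visits: 150 children per site, with temperature, blood film and fever history. No drug-related symptom enquiry is stated.
- End-of-season survey: all children, with examination, anthropometry, haemoglobin and blood samples. No symptom enquiry is stated. The list is not exhaustive, because the net-use check appears only in the nets section. The finding is therefore that the question is not scheduled.
- Serious adverse events: recorded for 18 months, so outside the gap.

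**Step 3. How many courses?** Inputs from Sample size: 1,500 children per arm per site, two sites.

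- Children per arm: 1,500 × 2 = 3,000.
- Courses per arm: 3,000 × 3 = 9,000.
- With a late enquiry (courses 1 and 2): 3,000 × 2 = 6,000.
- Without: 9,000 − 6,000 = 3,000, and 3,000 / 9,000 = one third. The count is the same on placebo.

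**Step 4. How long would recall be if the question were put at the survey?** The survey date is not given. The 2008 timetable gives July to November for "Administration of IPT and surveillance for malaria". Assume mid-month rounds and a survey between 15 November and 15 December.

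| Interval | Days |
| --- | --- |
| Burkina Faso, 15 Sep to 15 Nov / 15 Dec | 61 / 91 |
| Mali, 15 Oct to 15 Nov / 15 Dec | 31 / 61 |
| Between earlier rounds, e.g. 15 Aug to 15 Sep | 31 |

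Under these assumptions recall in Burkina Faso is about two to three times that after rounds 1 and 2 (61/31 ≈ 2.0; 91/31 ≈ 2.9). In Mali it is about one to two times as long.

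**Step 5. Does the window overlap transmission?** Table 1 gives a season to November at both sites, so most or all of the recall window falls within it. If IPT works, active children will have fewer febrile illnesses to recall. Equal recall length in the two arms does not remove that difference.

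**The case against.** The strongest reply is that what is missing is small. Every child is watched on days 0 to 3 of all three rounds and asked about late symptoms twice. Serious events are captured for 18 months. The duty to report possibly drug-related grade 3 events has no end date, and each site has a local safety monitor. A late reaction that brings the child to a project-staffed health centre may surface there, and a persisting sign or low haemoglobin may be found at the survey. All of this stands. It narrows the gap to non-serious symptoms for which no care was sought.

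A second reply is that the remedy is imperfect. Long recall means under-reporting, and prevented malaria may mask a drug excess. This also stands. An enquiry about four weeks after round 3 would match the earlier windows but would need an extra contact with every child.

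Several stronger readings are tempting, and the documents do not support them:

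- *The scheme fails the amendment's own aim.* The amendment says "This option provides the opportunity for monitoring adverse events in all study children". In context this contrasts all children with the random sample of 100 it replaced. That aim is met; a late enquiry after every course is not promised.
- *Course 3 matters most because prior exposure is greatest.* Nothing in the documents suggests that late non-serious reactions rise with course number.
- *The added question would deliver precise bounds or good power for late reactions.* Such figures would assume complete recall, over a window that may reach about 91 days and rests on an assumed survey date.
- *Staff would never ask.* The survey's listed content is incomplete, so only the absence of a scheduled question can be asserted.

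**Conclusion.** The point holds in a narrow form. The protocol schedules an all-child enquiry about symptoms after day 3 for two of three courses and none for the third: 3,000 of 9,000 planned courses in each arm. The count assumes full enrolment and that every child receives all three courses.

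The loss is limited to late, non-serious symptoms that do not lead to care. It falls on both arms by the same rule, so it reduces completeness and is no ground for alleging a biased comparison. The primary endpoint, its power and the recording of serious events are unaffected. Because the remedy costs so little it is worth making, but it ranks between an optional improvement and a mild recommendation.

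**What to change.** In the sections on safety of IPT and on the end-of-season survey, add that at the year-1 survey each family is asked about any possibly drug-related symptoms in the child since the third round. Then:

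- Report the answers by arm and site in the DSMB group summary, separately from rounds 1 and 2, because the recall window differs.
- Record the date of the survey contact, so that the actual recall interval can be stated.
- Tabulate fever-type symptoms apart from the rest, and say that the arm comparison is to be read with caution because IPT may prevent febrile illness.
- Label course 3 in any summary as having a longer recall period. If the question is not added, label it as having no scheduled enquiry after day 3.

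The cost is one question on the form of a survey already planned for every child, with no extra visit. The price in quality is longer recall, so under-reporting is likely, more so in Burkina Faso. If recall comparable to rounds 1 and 2 is wanted, the alternative is a separate contact about four weeks after round 3, at the cost of one more contact with up to 6,000 children.

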The main risk to this study is a severe drought which reduces malaria transmission to such an extent that there are insufficient cases of malaria to provide a clear result. This risk is mitigated to some extent by having three sites, each powered to give an individual result, as droughts in the Sahel are often focal. However, the risk is not completely prevented by utilizing three sites as a very severe drought might affect countries across the Sahel and sub-Sahel. A second risk is that a civil disturbance at a critical time of the year could interfere with field work. This is unlikely as the three countries selected are currently stable, but this possibility cannot be excluded.

Technical concerns include the possibility that IPT might be perceived to be harmful, leading to poor compliance. The SP + AQ combination causes minor side effects in some children and these could be perceived as being more serious than they are. A sound program of education about the trial, conducted in each site, before it starts should help to reduce this risk.

V. Monitoring, Evaluation, and Dissemination

To ensure that the project is conducted to the highest ethical standards, the proposal will be reviewed by ethics committees at each study site and at LSHTM. To ensure that the interests of study children are well protected, a DSMB will be established to monitor the trial. All serious adverse events and grade 3 adverse events which might be drug related will be reported to the DSMB, and the relevant ethics committee, within a time period agreed by the DSMB. Other adverse events will be summarized by group and reported to the DSMB at a frequency decided by the board. The DSMB will be supported by a local safety monitor at each site.

To ensure that the trials are conducted to the standards of Good Clinical Practice (GCP), a trials monitor will be appointed. He or she will visit each site before the trial starts, on at least one occasion during the collection of data and at the end of the trial.

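### For non-serious events after day 3 of rounds 1 and 2, the only enquiry described asks families to screen symptoms by suspected cause before anything is recorded, so unrecognised drug effects may be missed

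*Combined protocol and SAP*

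**What the plan says.** Section IV, Safety of IPT with SP and AQ, sets out three streams of safety data.

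- **Days 0 to 3 of each round.** "Safety of SP and AQ will be monitored in all children on days 0, 1 and 2 of treatment administration and on day 3", the day after the last dose. No restriction by cause is stated.
- **Between rounds.** At rounds 2 and 3, "the families of each study child will be asked whether the child has had any symptoms that might have been drug related" since the previous administration round. The amended text in the protocol amendments has the same wording.
- **Serious events.** "Serious adverse events, including deaths and hospital admissions, will be recorded throughout the 18 months of surveillance". The next sentence adds: "The likely relationship of the adverse event to drug administration will be determined according to standard criteria".

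Section V (Monitoring, Evaluation, and Dissemination) then covers reporting: "Other adverse events will be summarized by group and reported to the DSMB at a frequency decided by the board".

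The other planned contacts are health-centre visits for fever, home visits for blood films and the end-of-season survey. They are described as serving malaria detection, blood sampling, examination and net use. None is described as an adverse-event enquiry.

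**The concern.** The trial is placebo-controlled and takes steps to protect blinding, including ten randomization groups. In such a design, whether a symptom is drug related can be learned by comparing its frequency between arms. That requires symptoms to be recorded before anyone judges their cause.

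The between-round question reverses that order. A parent thinking back over about a month is asked only for symptoms with a possible link to the drug. A rash, jaundice or weakness without fever that the family attributes to something else has no described route into the safety data, unless it becomes serious. Once withheld, it cannot be recovered by the later relationship assessment or by the summaries by group for the DSMB.

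At stake is the completeness of the delayed, non-serious safety profile of a preventive drug given to children. Section VI makes consideration of the intervention depend partly on the absence of serious side effects, and those are captured separately. This point therefore concerns the milder, delayed part of the profile.

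**Working it through.** The documents state no adverse-event rate, no safety power and no reporting fraction, so there is no figure of the plan's own to reproduce. The check has three parts.

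**1. Coverage, from the text**

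| Event | Planned capture | Filtered by family's view of cause? |
|---|---|---|
| Any, days 0–3, all rounds | Monitoring of all children | Not stated |
| Serious, any time in 18 months | Recorded throughout | No |
| Non-serious, after day 3 of rounds 1 and 2 | One question at the next round | Yes |

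The filter applies to the last row only. Non-serious events after day 3 of round 3 have no later round at which to be asked about, which is a separate matter.

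**2. What a filter could do to the comparison**

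Inputs: 3,000 children per arm pooled (1,500 per arm at each of two sites, Section IV, Sample size). Everything else is assumed:
- background risk b = 5%
- drug-caused excess e = 2 percentage points
- share of background symptoms reported, sb
- share of drug-caused symptoms reported, sd

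Then p0 = b·sb and p1 = b·sb + e·sd.

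Power = Φ[(p1 − p0 − 1.96·SE0)/SE1], where SE0 = √(2·p̄(1 − p̄)/n), p̄ = (p1 + p0)/2, and SE1 = √{[p1(1 − p1) + p0(1 − p0)]/n}.

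Open question (sb = sd = 1): p1 = 0.07, p0 = 0.05, SE0 = 0.00613, SE1 = 0.00613. So (0.02 − 0.0120)/0.00613 = 1.30, and power is 90%.

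| sb | sd | p1 − p0 (points) | Risk ratio | Power | Drug-caused cases recorded (3,000·e·sd) |
|---|---|---|---|---|---|
| 100% | 100% | 2.0 | 1.40 | 90% | 60 |
| 75% | 75% | 1.5 | 1.40 | 80% | 45 |
| 50% | 50% | 1.0 | 1.40 | 62% | 30 |
| 25% | 25% | 0.5 | 1.40 | 36% | 15 |
| 50% | 80% | 1.6 | 1.64 | 94% | 48 |
| 20% | 80% | 1.6 | 2.60 | >99% | 48 |
| 50% | 20% | 0.4 | 1.16 | 16% | 12 |

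Three results follow.
- Drug-caused cases are lost whenever sd is below 100%.
- With equal shares, the absolute difference and power fall while the risk ratio stays at 1.40.
- With unequal shares, power and risk ratio can move either way. They rise if families pick out drug effects well, and fall sharply if they miss unfamiliar ones.

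The table applies the same shares in both arms. If families recognised active drug, for example from vomiting, the shares could differ by arm and the bias could go in either direction.

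**3. What an open question would bring in**

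IPT is meant to prevent malaria, whose symptoms overlap with possible side effects. The Sample size section uses 0.5 attacks per control child per year and a 20% reduction. Assume these attacks fall within five months and each produces a reported symptom. Two between-round months then carry 0.5 × 2/5 = 0.20 attacks per control child, and IPT removes 0.20 × 20% = 0.04, or 4 per 100 children. That is twice the assumed 2-per-100 drug excess, with the opposite sign. A single pooled count could therefore hide harm, so an open question needs a comparison symptom by symptom, with malaria separated.

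**The case against.** Five points can be made on the other side.

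**Serious events are safe.** Deaths and admissions are recorded for 18 months whatever the family thinks, and all-cause admissions are a secondary endpoint. This stands. A reader might infer that all delayed side effects pass through the family's filter, but the documents do not support that.

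**Under-counting is not shown.** The protocol gives one summary sentence, not the question script. The threshold of possible relation is low, and staff may probe more widely. This also stands, so the defect is a risk created by the wording.

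**A filter need not cost power.** Where families discriminate well, it raises power, as the table shows. A reader might infer a definite loss of power, but that holds only if drug-caused symptoms are withheld at least as readily as background ones. The gain, in turn, depends on accurate lay attribution, and the documents offer no evidence of that either.

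**The amendment summary is not proof of a contradiction.** It says "Adverse events that may occur after day 3 post IPTc will be recorded on day 0 of the next round of IPTc administration", with no restriction by cause. A reader might infer that the question defeats the amendment's own aim. That would rest on a change summary, and the operative amended text carries the filtered wording. The design point has to stand without it, and does.

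**Other parts of the plan do not add support.** The Challenges section worries that minor side effects may be perceived as more serious than they are, which suggests over-attribution if anything. The Section V statement that "All serious adverse events and grade 3 adverse events which might be drug related will be reported to the DSMB" governs reporting to the board, not what is asked of families.

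What survives is narrow. For one class of event the text has the family judge cause first, and nothing else described would catch what the family leaves out.

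**Conclusion.** The point holds in limited form: for non-serious events after day 3 of rounds 1 and 2, the described enquiry screens by suspected cause before recording, and drug effects the family does not recognise are liable to be missed.

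The size is unknown. Under the assumed 5% background and 2-point excess, power runs from 16% to above 99%, against 90% with an open question, depending only on which symptoms families report. That range shows the direction is undetermined; it is not an estimate of loss. The conclusion rests on the protocol sentence reflecting what is actually asked, and on no other adverse-event enquiry existing beyond those described.

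Priority is minor to moderate. The gap is confined to milder delayed events, and the remedy is cheap.

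**What to change.** In Section IV, Safety of IPT with SP and AQ, reword the between-round enquiry along these lines: at the second and third rounds, families will be asked about any symptom or illness the child has had since the previous round, regardless of suspected cause. Add that blinded study staff will judge relationship to the drug afterwards and record it separately.

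In the analysis plans, state that these events will be compared by arm symptom by symptom, with confirmed malaria episodes shown separately and events judged related shown as a subset.

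The contact already takes place with every study child, so no new visit is needed. If a structured symptom list is wanted, it would have to be written, since the documents describe none for days 0 to 3. The costs are more background symptoms to record and a less simple comparison than a single count.
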